# Effects of *Terminalia fagifolia* mart. extract combined with photobiomodulation on diabetic foot ulcers: protocol for a randomized single-blind clinical trial

**DOI:** 10.1007/s10103-026-04963-9

**Published:** 2026-07-25

**Keywords:** Diabetic foot ulcer, Chronic wounds, Low-level laser therapy, Phytotherapy, Ulcer healing

## Abstract

Diabetic wounds are characterized by persistent inflammation, prolonged healing time, and an increased risk of amputation. The use of natural compounds combined with established therapies can increase the effectiveness of treatments for these lesions. In this context, natural products have stood out as therapeutic adjuvants due to their anti-inflammatory, antioxidant, antimicrobial, and regenerative properties. *Terminalia fagifolia* Mart., a medicinal species native to the Brazilian Cerrado, has a rich phytochemical composition; however, its clinical potential in wound healing has not yet been investigated. This is the first clinical trial to investigate the potential synergistic effects of *Terminalia fagifolia* Mart. extract, alone or in combination with photobiomodulation, on the healing of non-infected diabetic foot ulcers. A total of 102 participants with type 2 diabetes and lower limb ulcers will be randomly allocated into three groups: G1 (Terminalia fagifolia Mart. + wound occlusion), G2 (GaAs 904, 10 J/cm² + Terminalia fagifolia Mart. + wound occlusion), and a control group using Endophoton KLD (GaAs 904) at a dose of 10 J/cm² + conventional dressing. One hundred and two volunteers will be recruited and treated on two non-consecutive days per week for 10 weeks, totaling 20 sessions. The primary outcome variable will be the rate of ulcer size reduction over the 10-week period. This study is expected to provide preliminary evidence regarding the safety, feasibility, and potential efficacy of the synergistic use of T. fagifolia Mart. extract combined with photobiomodulation in the treatment of diabetic foot ulcers.

**Clinical trial registration **

This study was registered at Brazilian Clinical Trials Registry (ReBEC) on December 27, 2023 (RBR-25ng5pt || https://ensaiosclinicos.gov.br/rg/RBR-25ng5pt).

## Introducion

Diabetes mellitus (DM) is one of the leading causes of lower-limb complications. Approximately one-quarter of ulcers fail to heal, thereby increasing the risk of amputation [1]. Even when healing is achieved, recurrence rates remain high, reaching 60% at 3 years and 65% at 5 years [2]. Following amputation, the mortality rate ranges from 50% to 68% within 5 years, exceeding that associated with some types of cancer [3]. This scenario, coupled with the increased risk of amputations and recurrent hospitalizations, imposes a substantial financial burden on healthcare systems [4].

Chronic hyperglycemia prolongs the inflammatory phase and consequently impairs wound healing in patients with DM [5]. This condition hinders the proper progression to subsequent healing phases, particularly the proliferative phase, which is characterized by fibroblast migration and proliferation as well as extracellular matrix deposition [6]. In this context, natural extracts have been explored as therapeutic adjuvants, as their bioactive compounds may exert anti-inflammatory, antibacterial, antioxidant, and regenerative effects [7].

Species of the genus *Terminalia*, such as *Terminalia bellerica* and *Terminalia chebula*, demonstrate relevant effects on tissue repair, including modulation of the inflammatory response, stimulation of collagen synthesis, acceleration of epithelialization, and antimicrobial activity [8, 9]. The Brazilian species *Terminalia fagifolia* Mart., found in the Brazilian Cerrado, is popularly known as “capitão,” “capitão-do-cerrado,” “capitão-do-campo,” and “mirindiba,” and possesses broad biological potential [10–11]. Like other species of the *Terminalia* genus, *T. fagifolia* exhibits antifungal, anti-inflammatory, hypoglycemic, antibacterial, antioxidant, anticancer, hepatoprotective, and cardioprotective properties. These effects have been attributed to its diverse chemical composition, characterized by a high concentration of secondary metabolites, which confer broad therapeutic potential to the extract [12–14].

Another treatment option is photobiomodulation (PBM), a safe, effective, and low-cost therapeutic approach [15]. The primary mechanism of action of PBM is associated with mitochondrial stimulation, with cytochrome c oxidase (COX) serving as its main chromophore and playing a key role in mitochondrial respiration [16]. Light absorption by COX increases adenosine triphosphate (ATP) production, stimulates the controlled formation of reactive oxygen species (ROS), and enhances mitochondrial respiratory efficiency [17, 18]. These effects can activate several signaling pathways, such as JAK/STAT, which play essential roles in modulating inflammation and tissue repair [19].

A study conducted with 60 rats evaluated a hydrogel dressing composed of cashew gum polysaccharide (POLI) and chitosan (CHI), combined with the application of PBM at 660 nm. Animals treated with the combined intervention exhibited greater wound contraction, increased collagen deposition, reduced focal necrosis, and earlier epithelialization [20]. Gonçalves et al. [21] demonstrated that the association of PBM with *B. oleracea* resulted in a significantly greater reduction in wound area compared to the control group, indicating a possible additive or synergistic effect between the interventions.

Considering the evidence available in the literature, the combination of natural compounds with established therapies may enhance the effectiveness of diabetic foot ulcer treatment. In this context, the combination of photobiomodulation, innovative dressings, and natural compounds represents a promising strategy for the development of more effective therapies in clinical practice. To date, no study has investigated the effects of combining *T. fagifolia* Mart. extract with PBM. To our knowledge, this is the first randomized, single-blind clinical trial designed to investigate the potential synergistic effects of *T. fagifolia* Mart. extract combined with PBM in patients with DFU.

Therefore, this clinical trial will evaluate the topical application of T. *fagifolia* Mart. extract and PBM individually, as well as their combination, to investigate potential synergistic effects on the healing of DFU. Thus, the hypothesis of this study is that the synergistic effect of T. *fagifolia* Mart. extract and PBM may accelerate the tissue repair process when compared to the isolated use of each therapy.

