### Sample size

The sample size was calculated using G*Power 3.1.9.4 software, based on the primary outcome of wound area reduction [25]. A repeated-measures ANOVA (F-test) was used to account for the interaction between within-subject factors (three time points: baseline, 5 weeks, and 10 weeks) and between-subject factors (three groups: CG, G1, and G2). The analysis considered a statistical power of 0.90, an alpha level of 0.05, and an effect size of 0.31. Based on these parameters, a total sample size of 93 participants was estimated. Assuming a 10% loss to follow-up, 102 volunteers will be recruited (34 volunteers per group).

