### Primary outcome

#### Ulcer reduction rate

The primary variable will be the rate of ulcer size reduction over 10 weeks. After the initial assessment, the DFUs will be identified, and the area will be photographed alongside a paper ruler, which will serve as a calibrator for the ImageJ software (Fig. 2) [28, 29]. DFUs will be assessed at three time points: pre-intervention (baseline), after 5 weeks (10 sessions), and after 10 weeks (20 sessions). The calculation of the reduction rate will follow the same parameters used by Ahmed and Irfan [30], represented by the formula: $$\:\frac{Af-Ai}{Ai}\:x\:100$$. Here, Ai and Af denote the initial and final ulcer areas, respectively. Ulcer area measurements will be performed by a blinded independent evaluator, who will be unaware of group allocation. The primary outcome will be compared between groups and across time points using repeated-measures analysis.

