### Statistical analysis

All statistical analyses will be conducted according to the intention-to-treat principle. Data will be tabulated in spreadsheets (Excel package) and analyzed using SPSS version 29 (Statistical Package for the Social Sciences). Sociodemographic data will be presented as descriptive statistics, absolute values and percentages, or mean and standard deviation (median and interquartile range). Normality will be assessed using the Kolmogorov–Smirnov test. The chi-square test will be applied for categorical data. To analyze differences between groups, a one-way ANOVA or the Kruskal–Wallis test will be performed. Intragroup analysis will be conducted using one-way repeated-measures ANOVA or the Friedman test. Statistical significance will be set at *p* < 0.05, and results will be presented in tables. The cumulative proportion of responders will be calculated considering a 50% healing rate, based on the article previously published by the group, and analyzed as described by Farrar et al. [22, 31]. In studies with graded outcomes, the mean difference between the curves of two groups represents the absolute risk reduction (ARR), from which the number needed to treat (NNT = 1/ARR) can be derived.

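### The hypothesis needs the combination to beat each single therapy, but every between-group test named, and the 90% power, concerns a three-group comparison without direction

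*Protocol article*

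**What the plan says.** The Introduction states that the combination "may accelerate the tissue repair process when compared to the isolated use of each therapy". Under Randomization, CG receives photobiomodulation, G1 the extract and G2 both, so the isolated therapies are CG and G1.

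Three places fix how the groups are compared:

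- **Ulcer reduction rate (primary outcome):** "The primary outcome will be compared between groups and across time points using repeated-measures analysis".
- **Statistical analysis:** "To analyze differences between groups, a one-way ANOVA or the Kruskal–Wallis test will be performed". Chi-square is added for categorical data, and significance is set at p < 0.05.
- **Sample size:** "A repeated-measures ANOVA (F-test) was used to account for the interaction between within-subject factors" (three time points) and the three groups. "The analysis considered a statistical power of 0.90, an alpha level of 0.05, and an effect size of 0.31", from which "a total sample size of 93 participants was estimated". After allowance for 10% loss, 34 per arm are to be recruited.

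None of these names a pair of groups, a direction, or a rule that G2 must beat both components. The one two-group quantity is the absolute risk reduction and number needed to treat for the secondary responder outcome. It is an estimate, not a test, and the pair is not named.

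**The concern.** A three-group test asks whether any arms differ. It has no direction and does not say which arm is responsible. A small p-value is as compatible with a poor CG and G2 = G1, or with G2 being worst, as it is with G2 beating both components.

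Two things are at stake. The first is inference: the trial can reach significance on every test it names without evidence on its own hypothesis, and the pair to emphasise could then be chosen after the data are seen. The second is size: the 90% power describes detection of any difference among three arms, whereas the hypothesis needs two separate wins, which is usually harder.

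**Working it through.** **Inputs from the Sample size section:** 3 groups, 3 time points, alpha 0.05, power 0.90, effect size 0.31 (read as Cohen's f), N = 93, which is 31 per arm. **Assumed, not in the document:** correlation rho = 0.5 between time points, normal data, common SD.

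**Step 1: reproduce 93.** For the between-factors test in a repeated-measures ANOVA:

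lambda = f² × N × m / (1 + (m − 1) × rho) = 0.0961 × 93 × 3 / (1 + 2 × 0.5) = 13.41, with 2 and 90 df.

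This gives power 0.907. N = 90 gives 0.897, so 93 is the smallest balanced total reaching 0.90. The group-by-time interaction formula, lambda = f² × N × m × epsilon / (1 − rho), would need only N = 30 at rho = 0.5 and epsilon = 1. It returns 93 at rho = 0 and epsilon = 0.5. Either way, the 90% belongs to an omnibus F-test.

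**Step 2: two scales for the effect.**

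- *Between-factors scale:* on each participant's mean over the three time points, f = 0.31 × √(3/2) = 0.380. Check: 0.380² × 93 = 13.4, as in step 1.
- *One-time-point scale:* f = 0.31 in a one-way ANOVA. Then lambda = 0.0961 × 93 = 8.94, and omnibus power is 0.753.

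**Step 3: convert f to gaps between arms, in SD units.**

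- One arm differs from two equal arms: d = 3f/√2, which is 0.805 (between-factors) or 0.658 (one time point).
- Equally spaced arms: adjacent gap f × √1.5, which is 0.465 or 0.380. The outer gap is twice that.

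**Step 4: simulate.** At least 100,000 trials per scenario with 31 per arm. Each trial has an omnibus F-test at 0.05 and pooled-variance t-tests of G2-G1 and G2-CG (90 df, two-sided 0.05). A joint win means that both favour G2.

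| True pattern | Omnibus significant: between-factors / one time point | Joint win: between-factors / one time point |
|---|---|---|
| G2 = G1, CG worse | 91% / 75% | 2.5% / 2.5% |
| G2 = CG, G1 worse | 91% / 75% | 2.5% / 2.5% |
| G2 worst, G1 = CG | 91% / 75% | 0% / 0% |
| G2 best, G1 = CG | 91% / 75% | 80% / 59% |
| Equally spaced, G2 best | 91% / 75% | 44% / 30% |

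The hypothesis is false in the first three rows and true in the last two. The omnibus column is the same throughout, so it cannot tell them apart.

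With all 34 per arm retained, the last two rows give joint wins of about 84% and 47% (between-factors) or 64% and 33% (one time point).

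**Step 5: size for 90% joint power when G1 = CG.** About 40 per arm (120 in all, before loss) on the between-factors scale, and about 59 per arm on the one-time-point scale. If the arms are equally spaced on the between-factors scale, the smaller gap of 0.465 alone needs about 98 per arm.

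**Step 6: if 0.31 is an interaction effect.** With change linear over time and contrasts taken on the change from baseline to week 10, joint power at 31 per arm is about 99% or more (G1 = CG) and 73% to 95% (equally spaced), for rho from 0 to 0.5.

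**The case against.** The strongest reply is that this is incompleteness, not error. An omnibus test followed by pairwise tests is a standard sequence, and with three groups it controls the familywise error. Gating the two contrasts on the omnibus test costs almost nothing: joint power moves from 80.4% to 80.0% on the between-factors scale and from 59.0% to 58.2% on the one-time-point scale. Follow-up contrasts are often left to a full protocol or analysis plan, which is not shown here. The trial also has other aims for which a three-group test is a reasonable start: Study design and recruitment proposes comparing the new dressing with photobiomodulation, and the abstract speaks of preliminary evidence.

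Much of this stands. It means the omnibus test need not be dropped and that G1 versus CG deserves its own place. It does not remove the mismatch. The article states one hypothesis, fixes tests that cannot answer it, and bases its sample size on one of them. Unspecified post hoc tests would supply neither a success rule nor the matching power.

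A reader might infer three stronger claims that the document does not support:

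- **That one-way ANOVA or Kruskal–Wallis is the only between-group test.** A repeated-measures analysis and chi-square are also named. They too are three-group comparisons as described.
- **That an omnibus p < 0.05 is the declared decision rule for the hypothesis.** No section says so; the tests are only listed.
- **That the true power is 59% and not 90%.** The 59% uses a scale on which the omnibus test itself has only 75% power, so it is not the scale that reproduces 93.

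**Conclusion.** The concern holds in this form: the tests named and the basis of the sample size do not match the stated hypothesis. An omnibus result would be significant in about 91% of trials (between-factors scale, rho = 0.5 assumed) or 75% (one-time-point scale) when G2 equals one component or is the worst arm. Requiring both contrasts would pass about 2.5% or 0% of those trials.

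The size of the power shortfall is uncertain, because the document gives neither the correlation nor an unambiguous meaning for 0.31. Joint power at 31 per arm is 80% or 44% on the scale that reproduces 93, 59% or 30% if 0.31 is a one-time-point effect, and higher, up to above 99%, if it is an interaction effect. The 80% and 44% concern the mean over the three time points. If 0.31 holds at each time point, an unadjusted contrast at week 10 alone falls on the one-time-point figures. No single one of these values should be presented as the trial's power. The inferential gap, by contrast, is present on every scale.

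**What to change.** Make these changes in the Statistical analysis and Sample size sections, before any unblinded analysis:

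1. Name two primary contrasts at week 10, G2-G1 and G2-CG, estimated from the primary repeated-measures model.
2. State that the hypothesis is claimed only if both favour G2 at two-sided 0.05. Because both must succeed, no alpha split is needed.
3. Keep the omnibus test as a first step if wished, but say that its significance alone does not support the hypothesis.
4. Report G1-CG as a separate comparison, since the Study design section also proposes comparing the new dressing with photobiomodulation.
5. Say that the 90% power refers to the omnibus F-test. State what 0.31 measures and the correlation used, and give the power of the joint rule under at least two patterns (G1 = CG, and equally spaced arms).

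The cost is about one paragraph of wording, with no new data and no change to treatment. The downside is that, on most readings of 0.31, the stated power becomes less favourable. If the sponsor wants 90% for the joint claim, more participants may be needed: about 40 per arm before loss in the G1 = CG case on the scale that reproduces 93, and more under the other patterns on that scale or on the one-time-point scale.

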## Methods

### Study design and recruitment

This is a randomized, single-blind experimental study with blinding applied to the evaluator. In this study, we propose a comparison between a new dressing and PBM in non-infected diabetic ulcers over a period of 10 weeks (20 interventions). *Terminalia fagifolia* Mart. sample was collected in Timon City, Maranhão State of Brazil, during a rainy summer to obtain the plant extract, that will be used at a concentration of 1 mg/mL, defined based on prior experimental optimization conducted by the research group, considering physicochemical stability and preliminary biological activity. The species was identified and the voucher deposited in the Delta do Parnaíba Herbarium (HDelta), at the Parnaíba Delta Federal University (n° 6979). Furthermore, the study was registered in the National System for the Management of Genetic Heritage and Associated Traditional Knowledge (SisGen) under number A7851F5. Detailed formulation parameters are currently under patent protection, and a comprehensive description of the standardization process will be reported in a separate study under peer review. Detailed formulation parameters are currently under patent protection, and a comprehensive description of the standardization process will be reported in a separate study under peer review. In the control group, GaAs 904 nm, 70 mW, and an energy density of 10 J/cm² (ENDOPHOTON KLD) will be used in pulsed mode, as described in a previous study [22]. This study was approved by the local Research Ethics Committee (Protocol 6.499.992) and the Brazilian Registry of Clinical Trials (ReBEC) (RBR-25ng5pt) and will be conducted in accordance with the Declaration of Helsinki and the SPIRIT [23] (Standard Protocol Items: Recommendations for Interventional Trials) and CONSORT [24] (Consolidated Standards of Reporting Trials) guidelines.

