### Randomization, allocation, and blinding

Participants will be assigned to one of three groups through an online randomization program [26]: G1 (*Terminalia fagifolia* Mart + wound occlusion), G2 (GaAs 904, 10 J/cm^2^ + *Terminalia fagifolia* Mart. + wound occlusion) and the control group (CG) will use Endophoton KLD (GaAs 904) with a dose of 10 J/cm^2^ + conventional dressing (Fig. 1). An independent researcher, not involved in participant care or outcome assessment, will be responsible for conducting the randomization process. Records and treatments will be placed in opaque, sealed envelopes. The study will adopt a single-blind design, in which the assessor will remain blind to the intervention received by each group until the conclusion of the clinical trial.

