## Intervention

### Control group

The wounds will initially be cleaned with saline solution and sterile gauze. During all sessions, both the therapist and the patient will wear protective eyewear. Treatment will be performed twice a week, totaling 20 sessions over 10 weeks. The probe will be positioned perpendicularly to the ulcer, allowing precise irradiation of the wound edges. In the internal area of the wound, the sweeping technique will be applied, in which the probe will be moved slowly over the entire surface of the ulcer in continuous, parallel movements, maintaining an approximate distance of 1 cm. The duration of each session will be automatically determined by the device based on predefined energy density parameters. At the end of each application, the ulcer will be covered with a conventional dressing, defined in this study as standard wound care consisting of sterile gauze associated with topical *Helianthus annuus* vegetable oil. Patients will be instructed to clean the wound and change the dressing daily, following standardized home aseptic care guidelines [27]. To ensure protocol standardization, all sessions will be performed by the same trained therapist, using the same equipment, application method, and parameters described in Table 1.

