### Intervention groups

DFUs will undergo standardized cleaning with isotonic saline solution, using aseptic technique and sterile gauze. After cleaning, group G1 will receive topical application of *T. fagifolia* Mart. extract, followed by sterile occlusion of the lesion according to the established protocol. In group G2, *T. fagifolia* Mart. extract will be applied after irradiation with PBM Endophoton KLD GaAs (904 nm, 70 mW, dose of 10 J/cm²), followed by sterile occlusion of the wound with sterile gauze. Treatment will be conducted twice a week, totaling 20 sessions over 10 weeks. To ensure protocol standardization, all sessions will be performed by the same trained therapist. Participants will be instructed to remove the previously applied extract at the end of the day, then clean the lesion with isotonic saline solution, and apply occlusion with a conventional dressing consisting of sterile gauze and *Helianthus annuus* vegetable oil on days without treatment sessions. A detailed description of the procedures applied to each group can be found in Table 2.

**Table 1 Tab1:** Photobiomodulation parameters of the Endophoton KLD device used in the protocol

Parameters	PBM 904 nm	Description
Operational mode	Continuous	Device Settings
Radiant power (mW)	70 mW	Device Settings
Full power (W)	0,07 W	Device Settings
Contact area (cm^2^)	0,001 cm^2^	Device Settings
Power density (W/cm^2^)	1,00 W/cm^2^	Device Settings
Pulse duration	100 × 10^− 9^s	Device Settings
Time (s)	2s	Device Settings
Energy density (J/cm^2^)	10 J/cm^2^	Device Settings
Application technique	Scan and point	No skin contact
Irradiated area	-	Dependent on the size of the ulcer area
Number and frequency of sessions	20 sessions twice a week	-

**Table 2 Tab2:** Description of therapeutic procedures in intervention groups

Procedure	Group G1 T. fagifolia extract	Group G2 PBM + T. fagifolia extract
Initial ulcer cleansing	Isotonic saline solution + aseptic technique + sterile gauze	Isotonic saline solution + aseptic technique + sterile gauze
Therapeutic application	Topical application of *T. fagifolia* Mart extract	GaAs 904 nm, 70 mW, 10 J/cm², followed by topical application of *T. fagifolia* Mart extract.
Irradiation technique	—	Probe perpendicular to the edges; scanning inside the ulcer; distance ≈ 1 cm
Wound occlusion	Sterile dressing	Sterile dressing
Frequency of sessions	2x/week	2x/week
Total sessions	20 sessions (10 weeks)	20 sessions (10 weeks)

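### The printed photobiomodulation settings contradict each other and do not reproduce the stated 10 J/cm²

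*Protocol article*

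**What the plan says.** Photobiomodulation (PBM) is given in CG, with a conventional dressing, and in G2, with the plant extract. G1 receives the extract without laser.

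- **Mode in the text.** Study design and recruitment, writing of the control group, says "GaAs 904 nm, 70 mW, and an energy density of 10 J/cm² (ENDOPHOTON KLD) will be used in pulsed mode".
- **Mode in Table 1.** The table reads "Operational mode Continuous" and also has a row headed "Pulse duration", with the value 100 × 10⁻⁹ s. It gives no pulse frequency or duty cycle.
- **Other Table 1 entries.** Power is 70 mW (repeated as 0.07 W), contact area 0.001 cm², power density 1.00 W/cm², time 2 s and energy density 10 J/cm². All are labelled as device settings.
- **G2.** Intervention groups specifies "irradiation with PBM Endophoton KLD GaAs (904 nm, 70 mW, dose of 10 J/cm²".
- **Delivery.** The Control group section says "The duration of each session will be automatically determined by the device based on predefined energy density parameters". Inside the wound the probe is swept over the surface, "maintaining an approximate distance of 1 cm". Table 1 likewise says there is no skin contact.
- **Which figures govern.** The same section has all sessions performed "using the same equipment, application method, and parameters described in Table 1".

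**The concern.** Power density is power divided by area, and energy density is power density multiplied by time. Table 1 prints all five quantities, so it can be checked against itself, and it fails. The emission mode conflicts both between text and table and within the table.

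PBM is the laser component of the comparator and one of the two components of G2. The trial's hypothesis is that the combination does better than either therapy alone. A result is useful to others only if the PBM exposure behind it can be stated and repeated. If the table meant to fix that exposure is inconsistent, a difference between arms with and without laser cannot be tied to the dose the article names.

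**Working it through.** **Inputs, all from Table 1:** power P = 0.07 W; area A = 0.001 cm²; printed power density D = 1.00 W/cm²; time t = 2 s; printed energy density E = 10 J/cm².

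**Step 1, power density.** P / A = 0.07 / 0.001 = 70 W/cm². Printed: 1.00 W/cm². Ratio: 70.

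**Step 2, energy density.** There are two routes from the printed entries:

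- D × t = 1.00 × 2 = 2 J/cm², which is 5 times below 10.
- P × t / A = 0.07 × 2 / 0.001 = 140 J/cm², which is 14 times above 10.

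Neither reproduces the plan's 10 J/cm².

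**Step 3, solving backwards for time.** E / D = 10 / 1.00 = 10 s. E × A / P = 10 × 0.001 / 0.07 = 0.143 s. Neither is 2 s.

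**Step 4, solving backwards for area.** D = 1.00 W/cm² implies A = 0.07 / 1.00 = 0.07 cm². E = 10 J/cm² in 2 s implies A = 0.07 × 2 / 10 = 0.014 cm². Neither is 0.001 cm², and the two differ from each other. Changing the area alone therefore cannot repair the table.

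**Step 5, innocent explanations.**

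- *Decimal slip in the area.* 0.01 cm² gives 7 W/cm² and 14 J/cm²; 0.1 cm² gives 0.7 W/cm² and 1.4 J/cm². Neither matches.
- *70 mW is a peak power in pulsed mode.* The time-averaged density is then the duty cycle × 70 W/cm². A duty cycle of 1/70 gives 1.00 W/cm² but only 1.00 × 2 = 2 J/cm². Reaching 10 J/cm² in 2 s needs 10 / 2 = 5 W/cm², a duty cycle of 5/70 = 1/14, and this contradicts the printed 1.00 W/cm². No duty cycle fits all entries.
- *2 s is per point, not per session.* Energy density at a point is still 2 or 140 J/cm². Repeated exposure of the same point could add up to 10 J/cm² (five exposures at 2 J/cm²), but the article states no repeats, and power, area and power density would still disagree.

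**Step 6, mode and geometry.** These need no arithmetic. The text says pulsed; the table says continuous and gives a pulse length. A contact area is listed for a technique without contact at about 1 cm, so the spot size at the wound, which the dose depends on, is unclear.

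**The case against.** The strongest reply is that the dose is defined after all. The 10 J/cm² target is the same in the Abstract, the Methods text, the Fig. 1 legend and Tables 1 and 2, and the Control group section makes energy density the input from which the device sets the duration. On this view Table 1 is only poor reporting. The first part stands: the nominal target is consistent, and a reader should not infer that the article states conflicting target doses. It does not remove the problem, because the same section says sessions use the Table 1 parameters, and those do not lead to the target. Nor is this a matter of a condensed article leaving detail to the full protocol, since these are values that the article prints.

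Four stronger readings are tempting, and the documents do not support them.

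- *Patients may receive 140 J/cm², so there is a shown safety hazard.* That figure treats the listed contact area as the irradiated spot, which a technique without contact does not justify. The 70 W/cm² and 140 J/cm² show that table rows disagree; they are not demonstrated exposures.
- *The fixed 2 s contradicts the device-set duration.* The text speaks of a whole session, while Table 1 lists point and scan application over an area that depends on the ulcer. The 2 s may be a time per point, so this is an ambiguity and not an established contradiction.
- *Every comparison with CG is uninterpretable.* G2 is described with the same device, wavelength, power, dose and therapist as CG. If the settings are identical, G2 versus CG holds PBM constant whatever its true dose. Randomisation and blinded area measurement are untouched.
- *PBM is all that the control arm receives.* CG also has saline cleaning and an oil dressing changed daily.

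**Conclusion.** The point holds. The emission mode is stated two ways. The printed power density differs 70-fold from the printed power and area. The printed time gives 2 or 140 J/cm² against a stated 10 J/cm².

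The consequence is limited but material. The dose delivered in two of three arms cannot be established or reproduced from the article, so effects in G2 versus G1 and in G1 versus CG cannot be attributed to 10 J/cm². G2 versus CG keeps its internal comparability on the assumption of identical settings in both arms, though the laser dose to which the extract is added remains unknown. The sample size and the planned tests do not depend on these figures.

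The conclusion rests on reading the Table 1 rows as printed and on the standard relations between power, area, time and energy density. It makes no claim about which entry is mistaken or about how the device will in fact be set.

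**What to change.** Reconcile Study design and recruitment, the Control group and Intervention groups sections and Table 1 against the device record. The items to settle are:

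- emission mode, and whether the pulse duration applies;
- irradiated spot area at the working distance;
- power density;
- time, and whether it is per point or per session;
- energy density.

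Then issue one table whose entries agree arithmetically, and report the settings actually used in CG and G2. Which values are right is for the investigators to determine; none is proposed here.

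The cost is small: a corrected table and matching sentences, plus a notification to the ethics committee if the approved protocol carries the same figures. The design, sample size and analysis need not change.
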